### Blinding

2.12

As it is impossible to blind the physicians delivering the intervention and participants receiving the intervention due to the nature of the interventions, we will only blind the assessors. The resident Essessors, blinded to the participants’ allocation and not involved in the intervention, will perform the evaluations of each outcomes in a separate place, prior to the interventions.

### Data collection and management

2.13

We will keep in touch with the participants from recruitment to 3 months after treatment to promote participant retention and complete follow-up. The patients will be able to contact researchers at any time to get information they need.

This study will utilize electronic CRF (e-CRF) using the internet-based Clinical Research and Trial management system, managed by the Korea Centers for Disease Control and Prevention. The standard operating procedure (SOP) will be distributed for reference to the study-related procedures, including writing the CRF, entering data, and educating the evaluator and investigators at each site. A data query will be issued for range checking of the data values. Data entered in the e-CRF will be cleaned, locked, and concealed from all investigators, except for the investigator in charge of data management.

### Statistical methods

2.14

Sociodemographic characteristics and treatment expectancy will be evaluated for each group. Continuous variables will be expressed as mean (standard deviation) or median (quartiles). Differences between the 2 groups will be analyzed using the Student *t* test. Categorical variables will be expressed as frequency (%) and will be analyzed using the Chi-squared test or Fisher exact test.

The endpoint of this clinical trial is the differences in changes in the continuous outcomes (NRS, VAS, NDI, NPQ, EQ-5D-5L, SF-12) at each time point compared to the baseline between the 2 groups. As the primary analysis, ANCOVA will be performed with factors that significantly differ between the 2 groups at baseline as covariates and the groups as fixed factors. As an additional analysis, a linear mixed model will be used to analyze the differences in the changes between visits and the trend of such changes. The linear mixed model will be processed with the mixed model for repeated measures. In addition, the areas under the curve (AUC) will be calculated at each time point after randomization for each outcome during the treatment period and through the entire study period. The Student *t* test will be used to compare the difference in AUC between 2 groups. Additionally, percentages of patients whose NRS and VAS for neck pain decreased by more than 50% from the baseline will be compared for each time point. The time since randomization to the improvement of neck pain, as determined by a drop in the pain indices by more than 50%, will be estimated using the Kaplan–Meier survival analysis. The curves will be compared using the log-rank test. Furthermore, hazard ratios will be compared using the Cox proportional hazard model.

In this study, we will perform both intention-to-treat (ITT) and per-protocol analyses, with ITT analysis as the primary approach. For PP analysis, participants who underwent 6 or more treatment sessions during the 4-week treatment period will be analyzed separately. Missing data in the principal ANCOVA analysis and the AUC analysis will be processed by multiple imputation. Missing time point data in the survival analysis will be censored. All statistical analyses will be performed using the SAS version 9.4 statistical package (SAS Institute, Cary, USA), and differences will be considered statistically significant when *P* < .05.

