### Participant timeline

2.2

On the first visit, the participants will sign an informed consent form (ICF) after receiving an explanation about the study. The examiner will screen the participants for eligibility per the inclusion/exclusion criteria. The participants will be randomized to the pharmacopuncture or the PT group during the second visit and undergo their respective treatments thereafter. The recruited participants will visit the facility 13 times, 8 of which will be treatment sessions (twice per week for 4 weeks). In-person or over-the-phone follow-up surveys will be conducted on weeks 5, 8, and 12 after treatment initiation. The schedule of enrollment, interventions, and assessments for the participants is shown in Table 1.

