### Sample size calculation

2.9

The null hypothesis of this study is that there will be no difference in the outcomes between the experimental and control groups when treating chronic neck pain. The hypothesis will be tested using analysis of covariance (ANCOVA) as the primary analytical test. The significance level will be set to α = 0.05 (2-tailed), with type 2 error (β) of 0.2 and a power of 80%. The sample required size was calculated based on a meta-analysis that had analyzed the effectiveness of pharmacopuncture compared to acupuncture or electropuncture therapy in patients with cervical spondylosis.^[12]^ Although the control group of this study differs from ours, we determined that we can utilize that study for sample size calculation based on their findings that the effectiveness of acupuncture in treating neck pain is equivalent^[21]^ or superior^[21,22]^ to that of PT. The mean difference in VAS between the pharmacopuncture and control groups based on this meta-analysis was 1.79 ± 2.74.^[12]^ When effect size is calculated based on this, the f-value is 0.33. Using the G∗Power software, version 3.1.9.4 (Franz Faul, Christian-Albrechts-Universität Kiel, Kiel, Germany), a total of 77 participants will be required. Assuming a withdrawal rate of 20%, we plan to recruit 100 participants.

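### Section 2.14 makes the endpoint six instruments at every time point, contradicting the single primary outcome elsewhere and leaving no one test to carry the 5% error rate

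*Protocol article*

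**What the plan says.** Four places in the protocol article bear on what the primary test is.

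- **Section 2.7.1** is headed as the primary outcome and gives neck-pain VAS. It names no visit and says only that patients mark the scale whenever they are assessed. The Discussion repeats that neck-pain VAS is primary, again without a time point. Sections 2.7.2.1 to 2.7.2.7 list NPQ, NRS, NDI, SF-12 and EQ-5D-5L among the secondary outcomes.
- **Section 2.9** states: "The null hypothesis of this study is that there will be no difference in the outcomes between the experimental and control groups". It names no instrument and no visit. It continues: "The hypothesis will be tested using analysis of covariance (ANCOVA) as the primary analytical test", at two-sided 0.05 with 80% power. The inputs are for VAS: "The mean difference in VAS between the pharmacopuncture and control groups based on this meta-analysis was 1.79 ± 2.74". The result is 77 evaluable patients and 100 recruited.
- **Section 2.14** states: "The endpoint of this clinical trial is the differences in changes in the continuous outcomes (NRS, VAS, NDI, NPQ, EQ-5D-5L, SF-12) at each time point". The next sentence makes ANCOVA the primary analysis without limiting it to an instrument or visit. The closing sentence applies P < .05 to all analyses. There is no hierarchy, no adjustment, and no statement that any test is exploratory.
- **Section 2.2** fixes the follow-up times: "In-person or over-the-phone follow-up surveys will be conducted on weeks 5, 8, and 12 after treatment initiation".

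**The concern.** The two accounts of the endpoint cannot both be followed. Under section 2.7.1 the trial is judged on one instrument. Under section 2.14 it is judged on six, and on either account the result is read at every visit. If VAS favours pharmacopuncture at week 5 but not at week 12, or the reverse, the text has no rule for whether the null hypothesis is rejected. A significant result at any visit could be reported as the primary finding, and the 5% in section 2.9 would no longer describe the chance of a false claim. The trial is meant to inform clinical and policy decisions, so what counts as success should be settled before the data are analysed.

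**Working it through.** **1. Does the plan's sample size belong to one test?**

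Inputs from section 2.9: VAS difference 1.79, SD 2.74, two-sided alpha 0.05, power 80%. Section 2.11 gives equal allocation.

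- d = 1.79 / 2.74 = 0.653, and f = d / 2 = 0.327 (the plan states 0.33).
- Power = P(F′ > F critical), where F′ is noncentral F with 1 and N − 2 − c degrees of freedom, noncentrality f²N, and c covariates (0 to 3 tried).
- f = 0.33 gives N = 75; f = 0.327 gives N = 76; f = 0.325 gives N = 77. The number of covariates makes no difference to N.
- 77 / 0.8 = 96.25, so 97, which the plan rounds up to 100.

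The stated 77 is reproduced to within two patients as the size for a single 0.05 test on VAS. With 100 × 0.8 = 80 evaluable patients, that test has about 82% power.

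**2. Error rate with VAS as the only primary outcome, tested at each stated follow-up**

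Three tests (weeks 5, 8 and 12), each at two-sided 0.05.

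- If independent: 1 − 0.95³ = 14.3%.
- If correlated: P(max |Z| > 1.96) for three equally correlated normal statistics, simulated with 200,000 replicates.

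| Assumed correlation between visits | Chance of at least one false positive |
|---|---|
| 0.3 | 13.6% |
| 0.5 | 12.5% |
| 0.7 | 10.8% |
| 0.8 | 9.9% |

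The documents give no correlation, so the range is an assumption. Table 1 is not shown, so on-treatment assessments cannot be counted. One further assessment, if assumed, would raise the range to 11.3% (correlation 0.8) to 17.4% (correlation 0.3).

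**3. Error rate if section 2.14 is taken literally**

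Six instruments × three follow-ups = 18 tests.

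- If independent: 1 − 0.95¹⁸ = 60.3%.
- If correlated at 0.8 down to 0.3, both between instruments and between visits: 25% to 54%.
- If all 18 statistics share one correlation of 0.8 down to 0.5: about 22% to 40%.

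**4. What controlling the error would cost if several tests stayed primary**

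Bonferroni, f = 0.327, 80% power, 20% withdrawal:

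| Primary tests | Alpha per test | Evaluable N | Recruited N | Power per test with 80 evaluable |
|---|---|---|---|---|
| 1 | 0.05 | 76 | 95 | 82% |
| 3 (VAS, three visits) | 0.0167 | 102 | 128 | 68% |
| 18 (literal wording) | 0.0028 | 143 | 179 | 44% |

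The planned 100 patients support one primary test and not several.

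**The case against.** The strongest reply is that the protocol does have a primary outcome. Section 2.7.1 and the Discussion name neck-pain VAS, section 2.7.2 places the other five instruments among the secondary outcomes, and section 2.9 sizes the trial on VAS. On this view the sentence in section 2.14 is loose drafting, and its reference to a primary analysis ranks ANCOVA above the mixed model as a method. Section 2.14 also presents the mixed-model, AUC and responder analyses as additional, so they do not compete with the primary one.

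Most of this stands. A reader might infer from section 2.14 that the trial has no primary outcome, or that six co-primary instruments give a false-positive rate of 22% to 54%. The documents do not support that. The larger figures count instruments that the protocol itself calls secondary, and secondary tests at a nominal 0.05 do not inflate the error of a properly defined primary test.

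The reply does not remove the conflict between sections, and it does not supply a time point. With VAS settled as the instrument, section 2.14 still asks for a comparison at each visit, each at P < .05.

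A second reply is that the full protocol or an analysis plan may name the visit. That is possible, and a time point merely left out of an article would not be a finding. Here, however, the article states a rule, every time point, and that rule does not fit the single test for which the trial is sized.

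**Conclusion.** The point holds as an inconsistency with a measurable consequence. Section 2.14 contradicts sections 2.7.1 and 2.9 and the Discussion on what the endpoint is, and no single confirmatory test can be read from the text. The firm size is a family-wise error of about 10% to 14% instead of 5%, for VAS at the three stated follow-ups. It assumes equal correlations of 0.8 to 0.3 between visits and no further assessments. The error is higher if the six-instrument wording is followed, but that figure describes the wording and not the evident intent. The sample size is not at fault: it is right for one VAS test.

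**What to change.** Before any outcome analysis, reword section 2.14 and the null hypothesis in section 2.9 to say the following:

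- The single primary test is the between-group difference in change from baseline in neck-pain VAS at one pre-specified time point, by ANCOVA at two-sided 0.05.
- All other time points, instruments and analyses are secondary and support no confirmatory claim.

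The sponsor should choose the time point. The first assessment after the four-week course is one example; any single visit fixed in advance cures the defect. The deadline is the first look at outcome data, not unblinding, because section 2.12 blinds only the assessors.

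The change is to wording alone: no extra patients or measurements, and the planned 100 remain adequate. What the sponsor gives up is a claim based on any one of several time points.

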### Data monitoring

2.15

The data monitoring will be performed to examine the safety of participants and the clinical data's completeness. This monitoring will be done by comparing the CRF and the source documents and by reviewing participants’ safety data. Routine monitoring visit will be conducted 4 times, and closing-out visit will be done once at each site during the trial. Trial steering group will meet to review conduct throughout the trial period once every 2 months. The data monitoring committee was not organized as no severe AE regarding pharmacopuncture or PT previously reported are expected to occur. The interim analysis will not be done in this study.

### Stopping rules

2.16

The trial might be discontinued at any point upon discovery of an unexpected, evident or unacceptable risk for participants, or upon the occurrence of serious adverse events, presumed to be related to pharmacopuncture or PT, in more than 25% of the participants.^[23]^ The PI would make the final decision if to discontinue the study.

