### Randomization and allocation concealment

2.11

A statistical expert will randomize an equal number of patients (n = 50, each) into 2 groups, using a random table generated by the nQuery Advisor (Statistical Solutions Ltd., Cork, Ireland) 7.0 (or SAS 9.0 (SAS institute, Cary, USA) or SPSS 21.0 (SPSS Inc., Chicago, USA)) software. The randomization results will be delivered to each institution in sealed opaque envelopes to be stored in a double-locked cabinet. The investigator will provide an adequate explanation of the trial, and each patient that meet the inclusion and exclusion criteria and voluntarily sign the consent form will open a randomization envelope to be randomly assigned a subject number. The investigator will record the assigned random number for each patient on the patient's electronic chart.

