### Harms

2.17

To evaluate the safety, both the pharmacopuncture and PT groups will undergo blood test (white blood cell, neutrophil, lymphocyte, monocyte, eosinophil, basophil, red blood cell, hemoglobin, hematocrit, mean corpuscular volume, mean corpuscular hemoglobin, mean corpuscular hemoglobin concentration, platelet, erythrocyte sedimentation rate, total protein, albumin, total bilirubin, alkaline phosphatase, aspartate aminotransferase, alanine aminotransferase, gamma-glutamyl transpeptidase, and C-reactive protein) before treatments initiation and after the last treatment. The collected blood samples will be discarded immediately after analyzing the results. Matters pertinent to biological samples disposal will adhere to the SOP presented by the medical laboratory team. All adverse events reported during the study period will be collected, and the percentage of patients who develop an adverse event will be calculated for each group. The incidence of adverse event in the 2 groups would then be compared using the Chi-squared test or Fisher exact test.

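### The 25% serious-adverse-event stopping boundary names neither arm nor denominator, and any pooled count dilutes harm confined to one arm

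*Protocol article*

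**What the plan says.** Section 2.16 (Stopping rules) has two limbs. The first is discretionary: "The trial might be discontinued at any point upon discovery of an unexpected, evident or unacceptable risk for participants". The second is numeric: "upon the occurrence of serious adverse events, presumed to be related to pharmacopuncture or PT, in more than 25% of the participants". Both are permissive, and the section ends: "The PI would make the final decision if to discontinue the study". The numeric limb carries a literature reference.

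Section 2.15 (Data monitoring) explains why there is no independent committee: "The data monitoring committee was not organized as no severe AE regarding pharmacopuncture or PT previously reported are expected to occur". It does provide for monitoring of safety data, four routine visits and a close-out visit per site, and regular meetings: "Trial steering group will meet to review conduct throughout the trial period once every 2 months". No interim analysis is planned.

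Three other sections bear on how the 25% could be counted. Section 2.11 states that a statistician "will randomize an equal number of patients (n = 50, each) into 2 groups". Section 2.17 (Harms) says that "the percentage of patients who develop an adverse event will be calculated for each group". Section 2.12 (Blinding) says "we will only blind the assessors".

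**The concern.** The rule counts persons rather than events, but two things are left open. One is the arm: pooled or separate. The other is the denominator: the planned 100, those enrolled so far, or those treated so far. No minimum count is given either. These choices lead to quite different rules.

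Naming both treatments and then referring to participants as a whole points to a pooled count. One arm receives herbal extracts at acupoints. The other receives physical therapy such as heat, traction or electrotherapy. Their risks differ in kind, so a related-SAE signal would most plausibly appear in one arm, and a pooled percentage then averages it with the unaffected arm. With no monitoring committee and the final decision resting with the principal investigator, a usable number would help. What is at stake is patient safety during the trial, not the primary comparison.

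**Working it through.** The plan gives no operating characteristics for this rule and no expected SAE rate, so there is no stated probability to reproduce. The inputs from the documents are the 25% threshold (2.16), 100 participants (2.1) and 50 per arm (2.11). The SAE rates p below are assumptions, meaning the probability that a participant has at least one related SAE. Participants are taken as independent, and in running counts each outcome is taken as known when the participant is counted.

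**1. Pooled, against the planned 100.** More than 25% of 100 is at least 26 people. If all are in one arm, that is 26/50 = 52% of the arm. P(X ≥ 26) with X ~ Binomial(50, p):

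| One-arm rate p | Other arm 0% | Other arm 2% | Other arm 5% |
|---|---|---|---|
| 30% | 0.0009 | 0.0035 | 0.015 |
| 40% | 0.057 | 0.107 | 0.21 |

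At p = 50% with none in the other arm the probability is 0.44, and at 60% it is 0.90. An 80% chance of crossing needs p of about 57%.

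**2. Pooled, running count.** Here the 25% applies to everyone enrolled so far, checked after each participant, with the two arms of 50 in random order and harm in one arm only. Probability that the count ever exceeds 25%:

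| One-arm rate p | No minimum | At least 3 affected | At least 20 enrolled |
|---|---|---|---|
| 10% | 0.16 | 0.02 | 0.001 |
| 30% | 0.53 | 0.31 | 0.16 |

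Without a minimum, a single event among the first three participants already crosses the boundary (1/3 > 25%). The column with no minimum therefore largely reflects early chance.

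**3. By arm, fixed count.** More than 25% of 50 is at least 13. P(X ≥ 13) is 0.78 at p = 30% and 0.99 at 40%. An 80% chance is reached at p of about 31%.

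**4. By arm, running count with at least 3 affected.** The result depends on how often the count is checked. How many participants fall between two meetings is not stated, so a range is shown (exact recursion to n = 50):

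| One-arm rate p | Check every 1 | Every 5 | Every 10 | Every 25 |
|---|---|---|---|---|
| 10% | 0.11 | 0.09 | 0.08 | 0.01 |
| 15% | 0.31 | 0.27 | 0.22 | 0.08 |
| 30% | 0.93 | 0.91 | 0.89 | 0.83 |

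The like-for-like comparison at p = 30% is between running counts with at least 3 affected, checked after every participant: 0.31 pooled against 0.93 by arm.

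**5. Review at 2 affected in one arm.** P(X ≥ 2) = 1 − (1−p)^50 − 50p(1−p)^49. This gives 0.09 at 1%, 0.26 at 2%, 0.72 at 5% and 0.97 at 10%. The count is cumulative, so sparser checks delay the trigger but do not lower these figures. If both arms share the same low rate, the chance of at least one review is 1 − (1 − 0.0894)² = 0.17 at 1% and 1 − (1 − 0.264)² = 0.46 at 2%.

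**The case against.** The strongest reply is that the discretionary limb already covers this. A related-SAE rate of 30% or 40% in one arm of a neck-pain trial would be an unacceptable risk on any view, and the investigator may stop for that at any time. Safety-data monitoring, site visits, two-monthly steering meetings and an independent audit add further oversight. This stands. A reader might infer that the trial has no effective protection against harm in one arm. The documents do not support that.

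A second reply is that the rule may be applied at any point, which fits a running count at least as well as the planned 100. This also stands. A reader might take 0.0009 as the rule's behaviour and conclude that the boundary would almost never be crossed. That holds only for the fixed base of 100 and the lower rates. On a running pooled count the figure at 30% is 0.16 to 0.53. What survives is that every pooled version averages in the unaffected arm.

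Third, the cited reference or the full protocol (version 1.5) may define the count. Neither is at hand, so the reason for choosing 25% is not judged here. The sentence as published still fixes a number that can be read in several ways.

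Fourth, the low-count review is an addition, and clarifying the 25% alone achieves little at moderate rates. That is correct, and it is why the review is proposed.

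**Conclusion.** The point holds as a modest patient-safety improvement. The only numeric boundary leaves arm and denominator open, and on any pooled reading it is a poor detector of harm confined to one arm. At an assumed 30% one-arm rate with none in the other arm, the crossing probability runs from 0.0009 to about 0.53 depending on the base and minimum chosen. That spread itself shows that the rule is not fixed. The sizes rest on assumed SAE rates, independence between participants and full arms of 50. No estimate, type I error or power is touched, and the other safeguards remain.

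**What to change.** In section 2.16:

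- Keep the discretionary limb unchanged.
- State the 25% limb separately for each arm, with participants treated to date in that arm as denominator and at least 3 of them with a related SAE.
- Add a steering-group safety review, not an automatic stop, once 2 participants in one arm have had a related SAE.
- Tabulate these counts by arm at the existing two-monthly meetings and keep them from the blinded assessors.

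This fits the plan, since section 2.17 already reports adverse events by group. The review does most of the work (0.72 at a 5% one-arm rate, 0.97 at 10%). The by-arm 25% limb alone stays weak at such rates, at best 0.11 at 10%.

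The cost is one or two sentences, slightly more tabulation, by-arm counts that must be kept from the assessors, and a possible unneeded review: about 17% at a 1% rate in both arms and 46% at 2%. If protocol version 1.5 already states arm and denominator, only the sentence in the article needs aligning.
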